#### Primary outcome

2.5.1

The primary outcome is the PUR incidence.

The incidence of postpartum urinary retention (PUR) will be evaluated in accordance with the following criteria, which are grounded in the diagnostic guidelines outlined in “Postpartum urinary retention: an expert review” published in the American Journal of Obstetrics and Gynecology.Overt PUR: Inability to void spontaneously within 6 h postpartum or within 6 h after removal of the indwelling catheter following cesarean section.Covert PUR: Post-void residual (PVR) urine volume ≥ 150 mL after spontaneous voiding.Persistent PUR: Requirement for an indwelling catheter or intermittent catheterization by the 3rd day postpartum.

Assessment time points are: the first urination after delivery, 6 h after delivery, the initial urination on the first day, and the second day following acupuncture. Meeting any of the aforementioned criteria at any assessment point will be considered as a positive PUR case.

The PVR of the bladder will be measured using an Ultrasonic Bladder Scanner (BVI-9400 BladderScan^®^, Verathon Medical Europe, Ijsselstein, The Netherlands). All BladderScan BVI-9400 devices will be calibrated annually according to the manufacturer’s guidelines. Operators must complete a standardized training program and pass a competency assessment before performing study measurements. To ensure accuracy, any PVR measurement ≥150 mL will be immediately rechecked by a second, blinded operator within 15 min. The average of the two readings will be recorded as the final PVR value. The recorded PVR of the bladder and whether catheterization was required will be documented. The specific measurement times are illustrated in Figure 3.

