##### Postpartum uterine contraction pain

2.5.2.3

The Visual Analogue Scale (VAS) will be employed to assess postpartum uterine contraction pain. The visual scale spans 10 centimeters, ranging from 0 to 10, where “0” represents a painless state, and “10” signifies the most unbearable pain. Scores will be assigned at specific time points, including 6 h after delivery, 2 h after acupuncture on the first day, and 2 h after acupuncture on the second day.

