### Statistical analysis

2.10

Demographic characteristics, general situations, and baseline conditions of the two groups will be compared and analyzed. For measurement data, an independent samples t-test or Wilcoxon rank-sum test will be employed, while χ^2^ test or Fisher test will be used for categorical data.

The incidence of PUR will be accurately assessed using Fisher’s exact test, and the relative risk (RR) along with the corresponding 95% confidence interval will be calculated. For other ordinal data, the Wilcoxon rank-sum test will be applied, while clinical counting data will undergo testing through the χ2 test. Postpartum depression and anxiety will be compared using Fisher’s exact test, and the RR along with the corresponding 95% confidence interval will be computed. Subject blinding effectiveness will be analyzed using the James Blinding Index. All statistical tests will be two-sided, and a *p* value less than 0.05 will be considered statistically significant for the tested differences.

For exploratory subgroup analysis, participants will be stratified into different subgroups based on age (< 40 years, ≥ 40 years), BMI (< 25 kg/m^2^, ≥ 25 kg/m^2^), duration of labor (< 700 min, ≥ 700 min), epidural anesthesia (with or without), vaginal midwifery techniques (forceps midwifery, fetal head attraction midwifery, fetal head rotation, perineotomy), gestational age (> 280 days, ≤ 280 days), and newborn birth weight (< 4,000 g, ≥ 4,000 g). The incidence difference between the two groups will be compared within each subgroup using the same statistical methods as mentioned above.

The primary analysis will follow the intention-to-treat (ITT) principle. Missing data will be handled using multiple imputation. A logistic regression model adjusting for study center will be used for the primary outcome. Secondary and subgroup analyses will apply Bonferroni correction for multiple comparisons.

GraphPad Prism 10.2 will be used for all statistical analysis.

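### Plain Bonferroni is named for the secondary analyses, although Holm's step-down method gives the same familywise control and never rejects less

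*Protocol article*

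**What the plan says.** All the relevant text is in section 2.10 of the protocol article.

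- The second paragraph names the tests, including those for ordinal outcomes, counts and depression. It ends with a general rule: "All statistical tests will be two-sided", and a p "value less than 0.05 will be considered statistically significant for the tested differences".
- The third paragraph introduces the subgroups as exploratory ("For exploratory subgroup analysis, participants will be stratified into different subgroups") and tests the treatment difference inside each one.
- The fourth paragraph sets the multiplicity rule: "Secondary and subgroup analyses will apply Bonferroni correction for multiple comparisons".

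There is a single primary endpoint (section 2.5.1: "The primary outcome is the PUR incidence"), and the multiplicity sentence does not cover it. The article gives no number of secondary comparisons and no adjusted threshold. It also does not say whether secondary and subgroup analyses are corrected as one set or two. An article may leave those details to the full plan, and I do not count their absence as a fault.

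**The concern.** Bonferroni holds every test in a family of m to 0.05/m. Holm applies that threshold only to the smallest p-value. It then tests the next smallest at 0.05/(m − 1), and so on, stopping at the first failure. Neither method needs an assumption about how the tests are correlated, and both keep the familywise error at or below 0.05. Bonferroni therefore gives up some power on the secondary outcomes and gets no better error guarantee in return.

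What is at stake is the chance of confirming a real effect on outcomes such as time to first void, pain, blood loss and depression score. The conclusion on urinary retention is not at stake.

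A smaller wording point goes with this. The 0.05 sentence has no exception and does not say that, for the corrected tests, it refers to adjusted p-values.

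**Working it through.** **There is no figure in the plan to reproduce.** The article gives neither a family size nor an adjusted threshold, so the counts below are assumptions.

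**Counting the secondary comparisons.**
- Section 2.5.2 gives 10: time to first void, first-void volume, feeling at first void, effective rate, pain at three times ("including 6 h after delivery, 2 h after acupuncture on the first day, and 2 h after acupuncture on the second day"), 24 h blood loss, and the depression scale at two times.
- Section 2.6 (Follow-up) adds 2 if its measures are treated as secondary: the 6–8 week urination score and the PFDI-20.
- The assumed range is therefore m = 10 to 12.

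**Bonferroni power for one comparison.** Take a comparison with 80% power at two-sided 0.05. Its expected z-value is 1.960 + 0.842 = 2.802. Under Bonferroni its power is Φ(2.802 − z), where z is the 1 − 0.025/m normal quantile.

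| m | Threshold 0.05/m | z | 2.802 − z | Power |
|---|---|---|---|---|
| 10 | 0.00500 | 2.807 | −0.005 | 49.8% |
| 12 | 0.00417 | 2.865 | −0.064 | 47.5% |

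**Why Holm never rejects less.** Its thresholds for m = 12 run 0.05/12 = 0.00417, 0.05/11 = 0.00455, and so on up to 0.05. Any p-value at or below 0.00417 passes whatever its rank, because every Holm threshold is at least that large. Suppose the two smallest p-values are 0.0040 and 0.0044. Bonferroni accepts only the first, since 0.0044 exceeds 0.00417. Holm accepts both, since 0.0044 is below 0.00455.

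**Average power per true effect, m = 12.** These are simulations with independent tests, each true effect having 80% power at 0.05.

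| True effects among 12 | Bonferroni | Holm | Gain (points) |
|---|---|---|---|
| 4 | 47.5% | 49.3% | about 2 |
| 6 | 47.5% | 50.6% | about 3 |
| 8 | 47.5% | 52.4% | about 5 |
| 12 | 47.5% | 58.0% | about 10 |

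A smaller simulation gave 53% for the row with 8 true effects; the difference is immaterial. With 6 true effects and a correlation of 0.3 between tests, the result was 47.4% against 50.5%, so moderate correlation hardly changes the comparison.

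**Error control.** With 6 of 12 effects true, the simulated familywise error was 2.6% under Bonferroni and 3.4% under Holm. Under Holm it was 3.9% with 4 true and 2.6% with 8 true. All are below 5%.

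**Splitting the loss.** With 8 true effects, power falls from 80% to 52.4% under Holm, which is 27.6 points. It falls a further 4.9 points under Bonferroni. Only the 4.9 points come from choosing Bonferroni over Holm. The 27.6 points buy real protection: twelve independent tests at an uncorrected 0.05 would have a familywise error of 1 − 0.95^12 = 46.0%.

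**The case against.** **Bonferroni is valid, so preferring Holm is a matter of taste.** The first half stands: Bonferroni controls the error and choosing it is not a mistake. The second half does not. Holm gives the same guarantee under the same assumptions and is at least as powerful in every data set, so this is a real if small improvement. Bonferroni keeps one advantage: its adjusted intervals are simpler. That has some weight because the article reports relative risks with 95% intervals, including for depression. However, the article nowhere says that those intervals will be adjusted.

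**The percentages are illustrative.** This stands. The count of 12 includes two follow-up measures listed outside the secondary-outcome section. Independence is also not literal, because the effective rate is a categorised form of first-void volume and the pain scale is repeated three times.

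**Stronger readings that a reader might infer.**
- *That section 2.10 contradicts itself.* One could argue that a secondary p of 0.01 is significant under the rule that a p "less than 0.05 will be considered statistically significant for the tested differences" but not after Bonferroni with 12 tests, so that significance could be chosen afterwards. The text does not support this. A general level followed by a specific correction is a usual construction, and it is coherent if adjusted p-values are compared with 0.05. Reading 0.05 as applying to unadjusted secondary p-values would leave the Bonferroni sentence with no function. The wording is ambiguous, not contradictory.
- *That secondary and subgroup tests form one pooled family.* Adding the 16 listed subgroup strata (6 × 2 + 4) to 12 gives 28 tests, a threshold of 0.00179 and power of about 37%. The sentence fits separate correction within each set equally well, so the 37% figure rests on an inference.
- *That the fall from 80% to 47% is the cost of Bonferroni.* Most of it is the cost of correcting for multiplicity at all.

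**Conclusion.** The point holds as a minor efficiency improvement. For the secondary outcomes, Holm dominates the plain Bonferroni correction that the article names. The gain is about 2 to 5 percentage points of power per true effect when 4 to 8 of 12 comparisons are real, and about 10 points when all are. These sizes assume 12 independent comparisons, each with 80% power at 0.05. That Holm never rejects less does not depend on those assumptions.

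The link between the 0.05 sentence and the Bonferroni sentence needs clarifying but is not an inconsistency. The test of the primary outcome is outside the correction and does not change. How the subgroups should be analysed is a separate question that this point does not address.

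**What to change.** In section 2.10, or in the statistical analysis plan before unblinding:

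1. Replace Bonferroni with Holm's step-down procedure for the secondary outcomes. Treat them as one family, list the comparisons it contains, and keep it separate from the exploratory subgroups.
2. State that for these tests the 0.05 level applies to the adjusted p-values. The primary outcome stays at a two-sided 0.05, and the general sentence can remain for the other tests.

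This costs two sentences and no new data. The calculation only requires sorting the p-values. The drawback is that Holm-adjusted confidence intervals are less simple than Bonferroni ones. If ordinary 95% intervals are reported beside Holm-adjusted p-values, the report should label the intervals as unadjusted.

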## Discussion

3

Urination is a complex process involving the coordinated actions of the cerebral cortex, spinal cord micturition center, peripheral nerves, and the lower urinary tract musculature (7). Disruptions to the muscle or nerve functions controlling urination during childbirth can impact normal micturition function, resulting in PUR (15). Preliminary clinical studies have explored acupuncture as a potential intervention for PUR, suggesting possible modulation of neurotransmitter pathways and improvements in urodynamic measures (16, 17). Preclinical work further reports that acupuncture may inhibit neuronal apoptosis, promote neurotrophic factor synthesis and secretion, support nerve repair, and thereby improve bladder function (18–20). In animal models, EA has been reported to activate afferent and efferent pelvic pathways, enhance detrusor contractility, and improve voiding-related outcomes (21). These mechanistic observations require confirmation in rigorously designed clinical studies.

In this trial, acupuncture is administered at three acupoints—GV20, CV3, and CV4—selected on the basis of traditional Chinese medicine practice and prior clinical use. Neuroanatomical hypotheses posit that the paracentral lobule contributes to voluntary micturition; its scalp projection approximates the vertex midline near GV20, and stimulation at GV20 may influence central pathways involved in voiding (22). Accordingly, needling GV20 may influence central pathways relevant to voiding. The urination activity of the bladder is regulated by lumbosacral circuits; parasympathetic (S2–S4) and sympathetic (T11–L2) outflow innervate the detrusor and internal sphincter. CV3 and CV4, located in the lower abdomen, receive segmental innervation primarily from T12–L4. Needling CV3/CV4 may modulate pelvic afferent–efferent signaling and support coordination of the sphincter and detrusor (23, 24). These mechanistic links remain hypothetical and are derived largely from physiological and preclinical observations. Accordingly, the present multicenter, randomized, sham-controlled trial will test whether electroacupuncture at GV20/CV3/CV4 facilitates spontaneous voiding and reduces post-void residual in PUR, while prospectively monitoring safety outcomes (25, 26)

Clinical research on acupuncture for PUR remains scarce internationally. A small clinical study suggested that acupuncture may alleviate urinary retention and facilitate catheter removal in some postpartum patients, potentially reducing exposure to indwelling-catheter discomfort and infection risk; however, the evidence is limited by nonrandom allocation, small sample size, single-center design, and short follow-up, resulting in low certainty (11). However, the study cited faces limitations such as a small sample size and the absence of random grouping, resulting in a low level of evidence. Urgent challenges persist in existing clinical research on acupuncture for PUR, including: 1. Lack of clarity in PUR diagnosis, with many studies focusing predominantly on overt PUR while overlooking the diagnosis and treatment of covert PUR, thereby posing potential risks to both short-term and long-term bladder function. The current evidence level for acupuncture treatment of PUR is suboptimal, and a dearth of multi-center, large-sample, randomized controlled clinical trials hampers the availability of high-quality data to support its efficacy.

To address the existing challenges in current clinical research, we have formulated a comprehensive strategy involving a multi-center, large-sample, randomized controlled clinical trial. This trial aims to assess the impact of EA intervention on both the incidence of PUR and the recovery of bladder function. Our investigation will encompass the three distinct categories of PUR, namely overt, covert, and persistent types. Additionally, we will explore the influence of EA on common postpartum conditions such as uterine contraction pain, postpartum bleeding, depression, and anxiety. A critical aspect of the study involves long-term observations through follow-up, where we will scrutinize the enduring effects of acupuncture on urination and pelvic floor function in postpartum individuals.

However, certain limitations are acknowledged in our study design. The nature of acupuncture treatment poses challenges to achieving practitioner blinding. Simultaneously, the administration of sham acupuncture may induce psychological effects on patients. The standardization of acupuncture points, applied uniformly across all subjects without syndrome differentiation, is another study limitation. Furthermore, a potential challenge lies in determining the willingness of postpartum patients to continue acupuncture treatment until the study’s conclusion and to actively cooperate with the follow-up process.

This multicenter, randomized, sham-controlled trial will rigorously evaluate whether EA reduces the incidence of PUR and improves early bladder recovery; the results will help determine the clinical value of EA and may inform the use of non-pharmacologic strategies in postpartum rehabilitation.
